### Other measures

Psychosocial measure are collected through researcher administered questionnaires to children. Quality of life is measured using the Pediatric Quality of Life Inventory (PedsQL) [31]; social acceptance is measured using the relevant domain from the Kidscreen-52 health questionnaire for children and young people [32] and body image is assessed using the Children’s Body Image Scale [33]. The pediatric preference-based utility instrument, Child Health Utility 9D [34] is also completed to inform the economic evaluation.

#### School level data

Data on participating schools are collected through a questionnaire administered to head teachers or a nominated representative. Information requested includes details on school food and physical activity policies and any relevant initiatives or programmes delivered through school.

### Process evaluation

Implementation fidelity is assessed throughout the intervention year using a range of methods including direct observation, logbooks, parent and school staff questionnaires, research staff experiences and qualitative evaluation. The methods are described in detail elsewhere [17].

### Justification of sample size

Sample size calculation is based on the primary outcome (BMI z-score). Further calculations were also performed to estimate power for the secondary outcome of percentage of children overweight or obese. Planned analysis of the WAVES study will compare outcomes for control and intervention schools at follow-up times, adjusting for baseline measurements. Therefore power calculations undertaken were based on repeated measures methods using estimates of correlation between before and after measurements. A modified version of the design effect [35] was used to estimate sample size and accommodate varying cluster sizes (using the estimated: mean cluster size (n = 25; SD = 23). For the primary outcome of BMI z-score, a follow-up sample size of 1000 children split across 50 schools gives the study greater than 90% power to detect a difference of 0.25 BMI z-score between intervention and comparator groups (equivalent to approximately 0.5 kg body weight for a 7-year old child) under all likely estimates of the intraclass correlation coefficient (ICC = 0 to 0.04, estimated correlation between before and after measures = 0.9 and estimated dropout rate = 20%). A change of 0.25 in BMI z-score has been shown to be associated with clinically detectable benefits in obese adolescents [36] and longitudinal studies demonstrate a linear relationship between BMI z-score in children as young as 7 and heart disease events in adulthood [4]. Under more conservative estimates for the ICC, this sample size would provide more than 80% power to detect a 0.125 difference in BMI z-score. A BMI z-score difference as low as 0.125 is the primary outcome of choice for other childhood obesity prevention trials [37]. Allowing for school drop-out (~8%), 54 schools were therefore invited to take part.

For the secondary outcome of percentage overweight/obese, this sample size (with an estimated correlation of before and after measures of 0.7 and an ICC of between 0 and 0.02) provides greater than 80% power to detect a difference in the change of proportion of children who are overweight/obese from baseline to follow-up in control compared to intervention schools of about 7% (exact value depends on baseline values). All power calculations were carried out in STATA using the clustersampsi function [38].

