The primary analysis will be a complete case analysis. However, missing data will be reported and associations between outcomes explored. Depending on the nature of these associations and the extent of the missing data, sensitivity analysis will be undertaken using multiple-imputation techniques.

The primary outcome and primary sub-group comparisons at both time points will be considered significant at the 5% level (and so 95% CIs reported); whereas other secondary outcomes will be deemed significant at the 1% level (and so 99% CIs reported). This difference in levels of significance, gives more weight to the primary outcomes.

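### The power stated for overweight/obesity fits a 5% test, but the outcome is tested at 1%, where the claim fails at the upper end of the stated ICC range unless prevalence is about 17.5% or lower

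*Protocol article*

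**What the plan says.** Justification of sample size (Protocol article) sizes the trial on BMI z-score and then adds a power statement for one further outcome, percentage overweight/obese, which it labels secondary. The claim is that the planned sample "provides greater than 80% power to detect a difference in the change of proportion of children who are overweight/obese from baseline to follow-up". The article puts the size of that difference at roughly 7 points and notes that the precise figure varies with the baseline. Two design inputs are named for this outcome: "with an estimated correlation of before and after measures of 0.7 and an ICC of between 0 and 0.02". The sample in question is "a follow-up sample size of 1000 children split across 50 schools". On method, the section adds only that "All power calculations were carried out in STATA using the clustersampsi function". It gives no significance level and no prevalence for this calculation.

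Planned statistical analysis sets two significance levels. The looser one is reserved as follows: "The primary outcome and primary sub-group comparisons at both time points will be considered significant at the 5% level". A stricter one governs the remaining outcomes: "whereas other secondary outcomes will be deemed significant at the 1% level (and so 99% CIs reported"). Outcome measures lists percentage overweight and obese among the secondary outcomes. Nothing in the article exempts it from the 1% rule or relates the power figure to that rule.

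**The concern.** A power figure has meaning only for the test that will be applied. If the figure was worked out at 5% and the outcome is judged at 1%, the trial has less power for a 7-point difference than the reader is told. The size of the gap can be seen without any trial input: a test with exactly 80% power at two-sided 5% has 59% at two-sided 1%.

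This is the only secondary outcome with its own power statement, and it is also one of the effectiveness measures in the economic evaluation. A reader who trusts the stated power could take a result that is not significant at 1% as fairly strong evidence against a 7-point effect, when the design may not support that.

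**Working it through.** **Inputs from the article.** 1000 children in 50 schools at follow-up, so m = 20 per school on average. This number is already net of dropout. Cluster size has mean 25 and SD 23, so CV = 23/25 = 0.92. Correlation r = 0.7; ICC 0 to 0.02; difference 7 points.

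**Assumptions.** Equal arms (500 children each), two-sided tests, and control prevalence of 20%, 25% or 30%, because the article gives none.

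**Formulas.**
- Design effect for unequal clusters: DE = 1 + ((CV² + 1)m − 1) × ICC. At ICC 0.02: 1 + ((0.8464 + 1) × 20 − 1) × 0.02 = 1.719. At ICC 0.01: 1.359. At ICC 0: 1.
- Variance factor for baseline adjustment (ANCOVA): 1 − r² = 0.51.
- SE = √{[p₁(1 − p₁) + p₂(1 − p₂)] × 0.51 × DE / 500}.
- Power = Φ(0.07/SE − z), with z = 1.960 at 5% and 2.576 at 1%.

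**Reproducing the plan's figure.** Take 25% against 18% at ICC 0.02. The sum of variances is 0.1875 + 0.1476 = 0.3351. SE = √(0.3351 × 0.51 × 1.719 / 500) = 0.0242, and 0.07/0.0242 = 2.89. Power at 5% is Φ(2.89 − 1.96) = 82%, and the difference detectable with 80% power is 6.8 points. This agrees with the stated power of more than 80% for about 7 points.

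**The same case at 1%.** Φ(2.89 − 2.576) = 62%.

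**ICC 0.02, by assumed prevalence:**

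| Prevalence | SE | Power at 5% | Power at 1% | 80%-power difference at 5% | 80%-power difference at 1% |
|---|---|---|---|---|---|
| 20% | 0.0219 | 89% | 73% | 6.2 points | 7.4 points |
| 25% | 0.0242 | 82% | 62% | 6.8 points | 8.2 points |
| 30% | 0.0260 | 77% | 54% | 7.3 points | 8.8 points |

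**Power at 1% across the stated ICC range:**

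| Prevalence | ICC 0 | ICC 0.01 | ICC 0.02 |
|---|---|---|---|
| 20% | 95% | 85% | 73% |
| 25% | 89% | 75% | 62% |
| 30% | 83% | 67% | 54% |

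**Break-even.** At 1% and ICC 0.02, power reaches 80% only if prevalence is about 17.5% or lower (82% at a prevalence of 17%, 79% at 18%).

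**Conversion that needs no prevalence.** Φ(1.960 + 0.842 − 2.576) = Φ(0.226) = 59%.

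**Sensitivity.** With a change-score variance factor, 2(1 − r) = 0.6, and ICC 0.02, power at prevalences of 20%, 25% and 30% is 84%, 76% and 70% at 5%, and 65%, 53% and 46% at 1%.

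**The case against.** The strongest reply is that the 5% level is inferred, not read. The article states no alpha for this calculation, and the fit to 5% is itself conditional. At 30% prevalence, or with a change-score variance at 25%, power at 5% and ICC 0.02 is already below 80% (77% and 76%). With the article's mean cluster size of 25 in place of 20, the 25% case gives 78%. So the fit suggests 5% but cannot prove it. This stands.

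Prevalence is also not given, and the article warns that the exact difference depends on baseline values. Its one numerical anchor is the outcome definition, BMI above the 85th percentile of the UK 1990 reference, which corresponds to 15% in that reference population. At 15%, power at 1% and ICC 0.02 is about 87%, so the claim would survive. Against this, the Background says that childhood obesity in England has risen over 20 years and that obesity prevalence doubles over the primary school years. That makes a value as low as 15% hard to assume, but the article has no figure to settle it.

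A reader might infer that the stated power holds only for a 5% test, or that the real power is some single value near 60%. The article supports neither. At ICC 0 the claim holds at 1% for all three assumed prevalences, and values near 60% belong to ICC 0.02 with prevalence around 25%. Nor does this show a slip in arithmetic: the stated figure can be reproduced, and the fault is that it does not match the test rule.

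Finally, the planned 99% confidence intervals and absolute effects will show the imprecision directly. That limits the risk of misreading but does not correct the power statement.

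**Conclusion.** The concern holds in a conditional form. The article claims more than 80% power over the whole ICC range of 0 to 0.02 without giving alpha or prevalence, and elsewhere sets a 1% test for this outcome. At 1%, the claim fails at ICC 0.02 for assumed prevalences of 20% to 30% (73% down to 54%), holds at ICC 0, and at ICC 0.01 holds at 20% but not at 25% or 30%. It survives the full ICC range only if prevalence is about 17.5% or lower.

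These figures rest on ANCOVA variance, equal arms, two-sided tests, a mean of 20 children per school and the normal approximation. A change-score variance makes the 1% figures worse.

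It would be wrong to conclude that the trial is too small. The numbers of schools and children rest on BMI z-score, which is tested at 5%, and overweight/obesity is listed only as a secondary outcome. This is worth correcting because two stated items do not fit together; it does not threaten the design.

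**What to change.** In Justification of sample size, state the alpha and the prevalence used for overweight/obesity, and restate the power at the 1% level over the stated ICC range. Possible wording: at the two-sided 1% level, with r = 0.7 and control prevalence of 30% down to 20%, power for a 7-point difference is about 83% to 95% at ICC 0 and 54% to 73% at ICC 0.02; at ICC 0.02 the study has 80% power for a difference of about 7.4 points (20% prevalence) to 8.8 points (30%). The prevalences here are illustrative and should be replaced by the authors' own.

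The change takes a sentence or two. It needs no more schools or children and leaves the primary outcome and the 1% rule as they are. The only cost is a less favourable stated figure.

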### Data quality and management

All study data are stored in a password-protected customised database, hosted by the University of Birmingham. Paper-based information is held in locked filing cabinets in the study office. For all data entry, a minimum 10% sample is checked to monitor error rates. Potential errors are identified and checked using a range of techniques. These include clinical and data-driven range checks, and cross validation between variables where a correlation would be expected and when the same information is obtained from different sources.

### Planned statistical analysis

Trial analyses will be undertaken after the second follow-up measures are completed and there will be no interim analyses.

The baseline pupil (including sex, ethnicity, deprivation [based on IMD scores derived from home postcode] anthropometric measures, dietary intake, physical activity levels, psychological variables) and school level characteristics (school size, ethnic mix of pupils and % eligible for FSM) will be summarised by control and intervention arms, using numbers and proportions, means and standard deviations or medians and inter-quartile ranges.

Analyses of outcomes will be by intention to treat. As randomisation will be at the school (cluster) level, appropriate statistical methods to account for the clustering within schools (detailed below) will be used in the analysis. Analysis of outcomes will be for both 3- and 18-month follow-up stages.

We will use a mixed model ANCOVA with follow-up outcome values as the dependent variable and baseline values and treatment arm as the independent variables, to investigate effectiveness. These will be fitted using mixed models in STATA to allow for clustering. We will allow for clustering at the school level and explore the possibility of allowing for an additional level of clustering at the class level.

The primary analysis will be adjusted for baseline values for all outcomes. Secondary analysis will additionally adjust for pre-specified baseline school and child level covariates. These will include school level factors which were used in the randomisation (school size, % pupils eligible for free school meals, ethnic mix of pupils) and pupil level factors (sex, baseline BMI z-score, ethnicity, deprivation from home postcode, baseline total energy intake and baseline total physical activity). We will not adjust for age as all children will be of a very similar age. We will adjust at the school and pupil level for both ethnicity and deprivation as the school population is expected to differ from the consented study population.

Outcomes are either binary (e.g. non-overweight vs. overweight), or continuous (e.g. BMI z-score or energy expenditure), and therefore either log or linear link functions will be used, with transformations where appropriate to accommodate any non-normality. All model assumptions will be checked. We will report both relative and absolute treatment effects.

The primary analysis will be a complete case analysis. However, missing data will be reported and associations between outcomes explored. Depending on the nature of these associations and the extent of the missing data, sensitivity analysis will be undertaken using multiple-imputation techniques.

The primary outcome and primary sub-group comparisons at both time points will be considered significant at the 5% level (and so 95% CIs reported); whereas other secondary outcomes will be deemed significant at the 1% level (and so 99% CIs reported). This difference in levels of significance, gives more weight to the primary outcomes.

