**Methods:**

This cluster randomised controlled trial is set in 54 primary schools within the West Midlands, UK, including a multi-ethnic, socioeconomically diverse population of children aged 6–7 years.

The 12-month intervention consists of healthy diet and physical activity promotion. These include: activities to increase time spent doing physical activity within the school day, participation in the ‘Villa Vitality’ programme (a programme that is delivered by an iconic sporting institution (Aston Villa Football Club), which provides interactive learning opportunities for physical activity and healthy eating), healthy cooking skills workshops in school time for parents and children, and provision of information to families signposting local leisure opportunities. The primary (clinical) outcome is the difference in body mass index (BMI) z-scores between arms at 3 and 18 months post-intervention completion. Cost per Quality Adjusted Life Year (QALY) will also be assessed. The sample size estimate (1000 children split across 50 schools at follow-up) is based on 90% power to detect differences in BMI z-score of 0.25 (estimated ICC ≤ 0.04), assuming a correlation between baseline and follow-up BMI z-score of 0.9. Treatment effects will be examined using mixed model ANCOVA. Primary analysis will adjust for baseline BMI z-score, and secondary analysis will adjust for pre-specified baseline school and child level covariates.

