### Outcome measures

For clinical effectiveness, the primary outcome is the difference in body mass index (BMI) z-scores (using the UK 1990 BMI reference curves for children [26]) between arms at 3- and 18-month follow-up post-intervention completion. Secondary outcomes include: i) anthropometric measures: percentage overweight and obese (defined as a BMI greater than the 85th percentile on the UK 1990 reference charts for BMI centiles for boys and girls), skinfold thickness at 5 sites (biceps, triceps, thigh, suprailiac and subscapular), waist circumference and percentage body fat; ii) blood pressure; iii) dietary energy (kJ per kg body weight per day), fat, sugar, fibre (g/day), and fruit and vegetable intake (g/day and portions); iv) physical activity energy expenditure (kJ per kg body weight per day), and time spent doing sedentary, light, moderate and vigorous intensity activity (min/day), v) psychosocial outcomes to assess the wider effects of the intervention, including benefits and potential harms: health related quality of life and body dissatisfaction, and vi) longer term clinical effectiveness at 27 months post intervention in Group 1 schools.

For cost-effectiveness analysis, the primary outcome is cost per Quality-Adjusted Life Year (QALY). Other analyses will include cost per effectiveness outcomes such as change in BMI z-score and change in proportion of overweight/obese. A longer term model-based evaluation will predict cost-per-QALY outcomes over a lifetime by linking a change in weight status in childhood to future health outcomes in adulthood.

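### The primary analysis of overweight/obesity adjusts for baseline yes/no status only, although continuous BMI z-score is available; this costs the equivalent of about 15–23% more children for that secondary outcome

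*Protocol article*

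**What the plan says.** Under Planned statistical analysis, outcomes are analysed with a "mixed model ANCOVA with follow-up outcome values as the dependent variable and baseline values and treatment arm as the independent variables". The rule is then made general: "The primary analysis will be adjusted for baseline values for all outcomes". Overweight is treated as a binary outcome ("Outcomes are either binary (e.g. non-overweight vs. overweight), or continuous (e.g. BMI z-score or energy expenditure"), with a log link for binary outcomes, and both relative and absolute effects are promised.

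Outcome measures defines the outcome as a cut on the BMI scale: "percentage overweight and obese (defined as a BMI greater than the 85th percentile". So the covariate that the general rule gives this outcome is baseline overweight/obese status. Justification of sample size supports that reading. It plans this outcome with an "estimated correlation of before and after measures of 0.7 and an ICC of between 0 and 0.02", whereas BMI z-score is planned with a before–after correlation of 0.9.

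Baseline BMI z-score appears as a covariate for other outcomes only in the secondary analysis, among the "pupil level factors (sex, baseline BMI z-score, ethnicity, deprivation from home postcode, baseline total energy intake and baseline total physical activity".

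**The concern.** A child just over the cut-off at baseline and a child far over it have very different chances of being over it at follow-up, and the same holds below the cut-off. Adjusting for status alone treats all children on one side alike, although the measurement that defines the status is in the data set.

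Overweight/obesity is the only secondary outcome with its own power statement. It also feeds the cost-effectiveness analysis, and like the other secondary outcomes it is declared significant only at 1%. Precision that could be recovered from data already collected is worth having here. What is at stake is efficiency, not validity.

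**Working it through.** **Inputs from the protocol article.** Follow-up sample of 1000 children in 50 schools, so 500 per arm and 20 per school; estimated cluster size mean 25, SD 23 (CV = 23/25 = 0.92); ICC 0 to 0.02 and correlation 0.7 for overweight/obesity; correlation 0.9 for z-score; more than 80% power for about 7 percentage points; 1% level for secondary outcomes.

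**Assumptions.** Baseline prevalence is not given; 20–30% is used, with 15–40% as a check. Baseline and follow-up z-scores are taken as bivariate normal, cut at the same point. Tests are two-sided. The level behind the power statement is not stated, so 5% is tried first.

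**Step 1: reproduce the plan's power.** The design effect is DE = 1 + ((1 + CV²)m − 1) × ICC = 1 + (1.8464 × 20 − 1) × 0.02 = 1.719. The effective number per arm is 500 / (DE × (1 − 0.7²)) = 500 / (1.719 × 0.51) ≈ 570. For 25% v 18%, power is 82% at the 5% level, which agrees with the stated figure. From 20% it is 89% and from 30% it is 76.5%, so the statement reproduces for a starting prevalence up to about 25%. For 25% v 18% at the 1% level, power is 62%.

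**Step 2: variance explained at correlation 0.9.** Baseline status explains φ², where φ is the correlation between the two yes/no statuses. Continuous baseline z explains R² = Var(P(status | z)) / Var(status), which equals the φ coefficient at latent correlation 0.9² = 0.81. The relative sample size is (1 − φ²)/(1 − R²).

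| Prevalence (assumed) | φ | φ² | R² | Relative sample size |
|---|---|---|---|---|
| 20% | 0.687 | 0.472 | 0.568 | 0.528/0.432 = 1.22 |
| 25% | 0.696 | 0.485 | 0.580 | 0.515/0.420 = 1.23 |
| 30% | 0.703 | 0.494 | 0.588 | 0.506/0.412 = 1.23 |

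A z-score correlation of 0.9 thus implies a status correlation of about 0.7, the value the plan uses. The ratio stays at 1.22–1.23 over prevalence 15–40%. It is 1.18–1.20 if the z-score correlation is 0.85, and 1.27–1.28 if it is 0.95.

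**Step 3: does a fitted model deliver this?** The table gives the variance of the log risk ratio under status-only log-link adjustment divided by its variance under each alternative, so values above 1 are gains. Each column rests on 1,200 simulated trials of 50 schools with 20 children, prevalence 25%, correlation 0.9. The log-link models were fitted with a Poisson working likelihood.

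| Model | ICC 0, no effect | ICC 0.02, no effect | ICC 0.02, z shift −0.2 |
|---|---|---|---|
| Log link, linear z only | 0.65 | 0.64 | 0.62 |
| Log link, status + linear z | 0.93 | 0.92 | 0.94 |
| Log link, status + piecewise z | 1.17 | 1.15 | 1.13 |
| Logistic, status, standardised | 1.00 | 1.00 | 1.00 |
| Logistic, z, standardised | 1.23 | 1.19 | 1.21 |

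Further simulations of the standardised logistic model, for risk difference or risk ratio, went as low as 1.15, with type I error near nominal. Some runs reached 1.25, slightly above the theoretical 1.23, so 1.15–1.23 is used as the range.

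**Step 4: power for 7 points, ICC 0.02, 20 per school.** Status adjustment uses residual variance 0.51; continuous adjustment uses 1 − R² from Step 2.

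| Comparison | 5%: status | 5%: z | 1%: status | 1%: z |
|---|---|---|---|---|
| 20% v 13% | 89% | 93% | 73% | 81% |
| 25% v 18% | 82% | 89% | 62% | 72% |
| 30% v 23% | 76.5% | 85% | 54% | 66% |

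If the gain is only 1.15, the effective number per arm for 25% v 18% is 570 × 1.15 ≈ 656, and power is about 87% at 5% and 70% at 1%.

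**The case against.** The strongest reply is that nothing here is wrong. Adjusting each outcome for its own baseline value is a standard rule, and the power statement was built on the same basis, so plan and power agree. The outcome is secondary, and it is a cut of a primary outcome that is already adjusted for continuous z-score. All of this stands and limits the weight of the point. It is not detail left to an unseen analysis plan, however, because the article fixes the rule for all outcomes.

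A second reply is that the secondary model already contains baseline BMI z-score, so an estimate adjusted for it will be produced. That is true, and the article does not say which model carries the 1% test. But the secondary model also needs baseline energy intake, from a 24-hour tick list partly completed by parents, and baseline physical activity, from a five-day monitor. Under the planned complete-case analysis, a child lacking either drops out. The loss described here concerns the minimally adjusted primary model.

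A third reply is decisive against a stronger reading. A reader might infer that adding z-score to the planned model recovers the whole loss at no cost. Step 3 shows otherwise: under the planned log link, a linear z term loses precision. Covariate and link have to change together.

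A reader might also infer a contradiction with the Abstract, which states: "Primary analysis will adjust for baseline BMI z-score". That sentence follows the BMI z-score sample size and in context describes the primary outcome. It does not override the Methods rule.

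**Conclusion.** The point holds as a matter of efficiency for one secondary outcome. Under the plan's correlation of 0.9, adjusting for status alone in the primary analysis of overweight/obesity costs the equivalent of about 15–23% more children. At 25% v 18% and ICC 0.02, the gain from using z-score is from 62% to about 70–72% power at the 1% level.

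This rests on bivariate normal z-scores, on a prevalence the article does not give (it hardly affects the ratio), and on the correlation of 0.9. The simulations used equal schools of 20, whereas the plan expects widely varying cluster sizes; the power figures allow for that through the design effect, but the simulated ratios do not. The documents do not support a reading that the planned analysis is biased or has the wrong type I error.

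**What to change.** State that the primary analysis of overweight/obesity adjusts for continuous baseline BMI z-score, with or without baseline status. Fit it with a logistic link that allows for school clustering, and standardise the result to a risk ratio and a risk difference, in place of the log link for this outcome. The standardised estimates supply the relative and absolute effects the article promises, whereas a bare logistic coefficient would change the reported measure to a conditional odds ratio. Do not simply add a linear z-score term to the log-link model. Word the Abstract so that its adjustment sentence is clearly about the primary outcome.

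No new data are needed. The cost is a changed link for this outcome, a small extra standardisation step whose standard errors must respect the schools, and the wording.

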#### Trial design and overview

The WAVES study is a cluster-randomised controlled trial. Primary schools (n = 54) are recruited from a multi-ethnic population within the West Midlands, UK. Randomization is at the level of the cluster (school). Data are collected at both the cluster (school) and within cluster (individual pupils and their parents) level. To test the effect of the intervention, a range of anthropometric and psychological data are collected (described in detail later) on children within participating schools. Baseline measures are undertaken when the participating children are in Year 1 (April to July; aged 5 to 6 years). Schools are then randomly allocated to either the usual practice or intervention arm. Schools in the intervention arm are asked to implement a 12 month, multifaceted intervention programme (details below) when children are in Year 2 (aged 6 to 7 years). The programme includes physical activity and dietary components, targeting the school and family environments and aims to help children maintain a healthy weight, thereby preventing overweight/obesity. Due to practical considerations, half the schools (Group 1) are recruited to commence the study in the 2011/12 school year and the remainder (Group 2) in the 2012/13 school year. First follow-up measures are undertaken immediately after the intervention year (September to December, when the children are in Year 3; aged 7 to 8 years) and second follow-up measures are undertaken 18 months post intervention (January to March, when the children are in Year 4; aged 8 to 9 years). Group 1 schools receive a third set of follow-up measures 27 months post intervention completion (September to December when in Year 5; aged 9 to 10 years). A summary of the study design and timelines is shown in Figure 1.

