### Method of random allocation and blinding

A blocked balancing algorithm is used to randomise schools to either the intervention or control arm [24,25]. This algorithm randomly selects one of a number of allocation designs which minimise the imbalance between covariate means. The covariates included are percentage of pupils within the school eligible for free school meals; percentage of South Asian pupils within the school; percentage of Black pupils within the school; percentage of White pupils within the school; and number of pupils within the school. Randomisation is undertaken after baseline measurements, and participating schools are then informed of allocation.

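### The primary model leaves out the school covariates used to balance the randomisation; to the extent that these predict outcome beyond baseline BMI z-score, its standard error is too large and its test conservative

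*Protocol article*

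**What the plan says.** Under Method of random allocation and blinding, the protocol article states: "A blocked balancing algorithm is used to randomise schools to either the intervention or control arm". It goes on: "This algorithm randomly selects one of a number of allocation designs which minimise the imbalance between covariate means". Five school-level covariates are listed. The list opens "The covariates included are percentage of pupils within the school eligible for free school meals; percentage of South Asian pupils within the school" and continues with the percentages of Black and of White pupils and the number of pupils.

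Under Planned statistical analysis, the main model is a mixed-model ANCOVA of the follow-up value on treatment arm and baseline value, allowing for clustering by school: "The primary analysis will be adjusted for baseline values for all outcomes". The abstract agrees: "Primary analysis will adjust for baseline BMI z-score, and secondary analysis will adjust for pre-specified baseline school and child level covariates". The secondary model adds school size, free-school-meal percentage and ethnic mix, which the article itself identifies as randomisation factors. It also adds child-level sex, ethnicity, deprivation, energy intake and physical activity.

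On timing, Trial design and overview says that "half the schools (Group 1) are recruited to commence the study in the 2011/12 school year and the remainder (Group 2) in the 2012/13". Under the allocation heading: "Randomisation is undertaken after baseline measurements, and participating schools are then informed of allocation". Study group is not among the listed balancing covariates, nor among the named adjustment covariates.

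**The concern.** Restricting the allocation removes most of the chance difference between arms in the balanced covariates. If those covariates also predict the outcome, the treatment estimate varies less from one possible allocation to another than under simple randomisation. A model without them does not register this. It leaves their contribution in the between-school residual and computes a standard error as if the arms could still differ on them. The reported interval is then wider than the design warrants, and the true type I error falls below the nominal 5%.

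At stake is precision in the primary analysis. This is a stated choice and not detail left for an analysis plan, because the article fixes the primary model and assigns the randomisation factors to the secondary one.

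**Working it through.** **Inputs from the article.** Justification of sample size gives 1000 children in 50 schools (20 per school), ICC 0 to 0.04, before–after correlation 0.9, and cluster size mean 25 with SD 23 (CV = 23/25 = 0.92). The 5% level with 95% intervals is under Planned statistical analysis. **Assumed, because not given:** outcome SD 1.0 (1.2 as a variant), and the share *f* of residual between-school variance that the five covariates explain.

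**Step 1: the plan's own power figure.** Design effect = 1 + [(1 + CV²)·m − 1]·ICC. At ICC 0.04 this is 1 + (1.8464 × 20 − 1) × 0.04 = 2.437. The effective number per arm is 500/2.437 ≈ 205. SE = √(1 − 0.9²) × √(2/205) ≈ 0.043. Power for 0.25 exceeds 99%, and power for 0.125 is 82.8%. Both stated claims (above 90% and above 80%) are reproduced at SD 1.0. At SD 1.2, power for 0.125 falls to 67.7%.

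**Step 2: how much the school covariates could explain.** School-level covariates can act only on between-school variance. Its share of the variance of a school mean is ICC / [ICC + (1 − ICC)/m].
- ICC 0.02: 0.02 / (0.02 + 0.049) = 0.29
- ICC 0.04: 0.04 / (0.04 + 0.048) = 0.455

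The omitted R² is *f* times this share. With near-perfect balance the unadjusted SE is too large by 1/√(1 − R²), and the true size is 2[1 − Φ(1.96/√(1 − R²))].

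| ICC | f | R² | SE too large by | True size |
|---|---|---|---|---|
| 0 | any | 0 | 0% | 5.0% |
| 0.02 | 25% | 0.072 | 3.8% | 4.2% |
| 0.02 | 50% | 0.145 | 8.1% | 3.4% |
| 0.04 | 25% | 0.114 | 6.2% | 3.7% |
| 0.04 | 50% | 0.227 | 13.8% | 2.6% |

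**Step 3: simulation of size.** Fifty schools in two waves of 25, five correlated covariates, allocation drawn from the best-balanced tenth of 200 candidates in each wave, 4000 runs. Size of the unadjusted test: 4.9% at R² 0, 4.1% at 0.10, 3.4% at 0.20, 2.1% at 0.30. The adjusted test stayed between 4.6% and 5.3%. The unadjusted sizes at 0.10 and 0.20 sit a little above the closed form, as expected when balance is good but not perfect.

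**Step 4: net effect on interval width, including the cost of the extra terms.** Ratio of adjusted to unadjusted width, with five covariates plus Group in the adjusted model, allocation from the best 5% of 200 candidates, 3000 runs:

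| ICC | f | Equal cluster sizes | CV 0.92 |
|---|---|---|---|
| 0.01 | 25% | 0.99 | 1.02 |
| 0.01 | 50% | 0.97 | 0.99 |
| 0.02 | 25% | 0.98 | 0.99 |
| 0.02 | 50% | 0.94 | 0.95 |
| 0.04 | 25% | 0.96 | 0.97 |
| 0.04 | 50% | 0.89 | 0.90 |

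With non-prognostic covariates the adjusted interval was 1.5–1.7% wider (equal sizes) or 2.8–4.5% wider (CV 0.92). A leaner run with four covariates and equal sizes gave 0.95 and 0.88 at ICC 0.04.

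**Step 5: power for 0.125** (SD 1.0, ICC 0.04, normal approximation, degrees-of-freedom cost ignored). Unadjusted against adjusted: 83% and 83% at R² 0, 84% and 86% at 0.10, 85% and 90% at 0.20. Power for 0.25 is above 99% either way.

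**The case against.** The strongest reply is that the harm is conditional. It needs between-school variance that remains after adjustment for a baseline correlated 0.9 with follow-up, and school covariates that explain it. The article quantifies neither. It also does not say that its ICC of 0 to 0.04 is a baseline-adjusted value. At ICC 0.01 to 0.02 with a quarter explained, adjusting changes the interval by only about −2% to +2%, and with unequal clusters it can lose precision. All of this stands. A reader might infer that the primary standard errors are too large as a matter of fact, and that precision is certainly being lost. The documents do not support that reading.

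A reader might also infer that study group restricted the allocation and is wrongly missing from every model. That is not supported either. Group is not among the five listed covariates. Separate allocation by group is only suggested by the term for blocking, the two start years and randomisation after baseline. The list of adjustment covariates is not worded as closed. This part is a query.

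A further reply is that the adjusted analysis is already pre-specified, so the dispute is only over which model is called primary. This stands only in part. The secondary model combines the school covariates with child-level dietary and activity-monitor data. The article names complete-case analysis for the primary analysis and keeps multiple imputation for possible sensitivity analysis. Unless those covariates are imputed, children without diet or monitor data would drop out of the secondary model. No planned model adjusts for the randomisation factors alone.

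**Conclusion.** The point holds in conditional form. The article restricts allocation on five school covariates and then leaves them out of the primary model. To the extent that they predict follow-up BMI z-score beyond baseline, the primary standard error is too large and the test conservative.

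Over the stated ICC range the effect of adjusting runs from nil or slightly adverse (interval about 1.5–4.5% wider if the covariates are not prognostic) to useful. At ICC 0.04 the interval is about 3–4% narrower if they explain a quarter of the residual between-school variance, and about 10–11% narrower if they explain half. These figures rest on assumed prognostic strength, an assumed balance criterion and simulated cluster sizes, so they are illustrative.

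It would be wrong to conclude that the trial's validity or its main power claim is threatened. The error is in the safe direction and power for 0.25 stays above 99%. The gain would matter mainly for an effect near 0.125, where the margin over 80% is thin. This is a worthwhile and cheap improvement, not a critical fault. Confidence is high that the covariates are omitted, and much lower about how much this costs.

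**What to change.** Define the primary model as follow-up BMI z-score on arm, baseline BMI z-score and the school-level balancing covariates (school size, free-school-meal percentage, ethnic mix), with a school random effect. The percentages of White, South Asian and Black pupils are nearly collinear because only the remaining category separates them from a fixed total. Their form should therefore be pre-specified, for example two of the three percentages. Keep the baseline-only model as a sensitivity analysis, and leave the child-level covariates in the secondary model.

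State whether allocation was done separately within Group 1 and Group 2. If it was, add Group to the primary model.

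The change is to wording only. The school covariates were needed for allocation, so they are held for every school. The cost is about five or six of roughly 48 school-level degrees of freedom, and a slightly wider interval if the covariates turn out not to be prognostic. The choice should be fixed before outcome data are analysed by arm; Trial status places analysis after June 2015.
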